## Abstract

**Background:**

The long-standing view that auditory verbal hallucinations (AVH) or hearing voices is a sign of schizophrenia has been challenged by research demonstrating that they lie on a continuum ranging from normal to pathological experience related to distress and need for care. Hearing voices is more prevalent in adolescence than in later life, and hearing voices during adolescence indicates a risk for severe psychopathology, functional impairments, and suicide later in life. While there is increasing evidence for the efficacy of cognitive behavioral therapy for voices (CBTv) in adults with schizophrenia, research on psychological treatments for youth with distressing voices has been scarce. The aim of the current study is to examine the efficacy of CBTv, delivered using smartphone-based Ecological Momentary Assessment Intervention (EMI) in a transdiagnostic sample of youth.

**Methods:**

This is a superiority randomized controlled trial comparing 8 weeks of CBTv-based EMI in addition to treatment as usual (TAU) versus TAU only. TAU covers both no treatment and any form of psychiatric/psychological treatment. In the EMI condition, participants will be prompted twice a day to complete an EMA survey, and receive one intervention proposal per assessment. One-hundred fifty-four youth aged 14–25 years with distressing voices will be recruited from psychiatric clinics, local private practices, internet forums, and advertisements in print and social media. Before and after the intervention phase, participants will undergo a 9-day EMA. Single-blinded assessments will be conducted at baseline (T0) and at 3-month (T1) and 6-month (T2) follow-up. The primary outcome is the distress dimension of the Auditory Hallucinations subscale of the Psychotic Symptom Rating Scales at T1. Secondary outcomes include perceived hostile intention, power, and dominance of voices, passive, aggressive, and assertive relating to voices, and negative core beliefs about the self.

**Discussion:**

Adolescence provides a crucial window of opportunity for early intervention for hearing voices. However, youth are notoriously reluctant help-seekers. This study offers a low-intensity psychological intervention for youth with distressing voices beyond diagnostic boundaries that, using a mobile technology approach, may match the treatment preferences of the generation of “digital natives.”

**Trial registration:**

German Clinical Trials Register DRKS00026243. Registered on 2 September 2021

**Supplementary Information:**

The online version contains supplementary material available at 10.1186/s13063-022-06846-0.

## Administrative information

The numbers in curly brackets in this protocol refer to SPIRIT checklist item numbers. The order of the items has been modified to group similar items (see http://www.equator-network.org/reporting-guidelines/spirit-2013-statement-defining-standard-protocol-items-for-clinical-trials/).

## Introduction

### Background and rationale {6a}

Auditory verbal hallucinations (AVH)—or hearing voices—are real-seeming auditory experiences in the form of spoken language that occur without a corresponding sensory input [1]. While hearing voices has long been considered a sign of a psychotic disorder such as schizophrenia, recent evidence suggests that they lie on a continuum ranging from normal to pathological experience related to distress and need for care [2]. Auditory hallucinations are more prevalent in adolescence (12.4%) than in later life (5.8% in middle and 4.5% in late adulthood) [3]. Although the majority of hallucinatory experiences in adolescence is transient [4], persistence can cause high levels of emotional distress and represent a risk marker for a wide range of negative outcomes in the long term (i.e., psychotic and non-psychotic mental disorders, multimorbidity, impairments in psychosocial functioning, and suicide [5–10]). Therefore, adolescence provides a crucial window of opportunity for early intervention for hearing voices in order to prevent suffering and disability in the affected young people and improve their life trajectories.

Cognitive behavioral therapy for psychosis (CBTp) is recommended for the treatment of individuals with psychotic disorders such as schizophrenia. In contrast to CBTp that targets positive symptoms (i.e., delusions and hallucinations) more broadly, CBT for voices (CBTv) is a symptom-specific development that focuses on key processes assumed to contribute to the emergence and persistence of distress and disability associated with voice hearing. Based on the continuum hypothesis of hearing voices [2], CBTv intervenes at the level of the individual “meaning-making” by targeting appraisals of voices [11] that are typically perceived as powerful, dominant, and intrusive [12, 13]. In more recent times, self-related and interpersonal variables have been included as additional or alternative treatment targets in CBTv approaches, as evidence indicates that people who are distressed by their voices typically feel powerless and inferior to their voices and respond relationally from a position of subordination (e.g., passively or aggressively) [12, 13]. Interestingly, relational experiences with the voices seem to mirror relational experiences within the wider social context, such that similar styles of relating are evident within the relationships with voices and other people [14–16]. A recent systematic review of eight randomized controlled trials (RCT) addressing hearing voices supports the general efficacy of CBTv in reducing voice-related distress or problematic behavior (e.g., compliance with voices), with effect sizes ranging from small (Cohen’s *d* = 0.44) to very large (*d* = 1.78). The change of the power imbalance between the voice and the voice-hearer was a common component of all included studies and may, thus, represent a key mechanism of change for all CBTv approaches [17].

These data suggest that CBTv could be a promising option for early intervention for young people with distressing voices. However, there are several challenges: First, the accessibility of CBTv is limited, due to scarcity of resources, geographic barriers, and ambivalent attitudes of patients and clinicians [18]. Second, although CBTv is potentially applicable to hearing voices beyond diagnostic boundaries [11, 18], its efficacy for voice-hearers with non-psychotic disorders or without any psychiatric diagnosis has rarely been investigated [17]. Third, as CBTv was developed for adults, little is known whether or not it is suitable for the treatment of young people with voices who might have specific developmental needs and distinct treatment preferences (e.g., flexible access, non-stigmatizing support, preference for self-reliance) [19, 20]. Fourth, young people with mental health issues show low use of face-to-face treatments [19, 21–23]. This has led to the request for a transformation of traditional mental health services to better match the needs and preferences of the youth [20]. The usage of digital technologies for treatment delivery may be part of the solution.

### Objectives {7}

The aim of the current study is to examine the efficacy of CBTv, delivered using smartphone-based Ecological Momentary Interventions (EMI) in a transdiagnostic sample of youth with distressing voices. The usage of smartphone-based EMI, also known as just-in-time adaptive interventions [24], provides several advantages: First, built upon Ecological Momentary Assessment (EMA; also called experience sampling method), the interventions can be individually tailored to the person’s momentary experiences and symptoms. Second, the interventions occur in the context of daily life, therefore bridging the gap between the clinical setting and the real world. Third, the usage of mobile technology for treatment delivery provides an opportunity for low-intensity and time- and place-unlimited support. This may be particularly relevant for young people who prefer short and uncomplicated interventions and find smartphones an appealing medium to deliver mental health treatments [25, 26]. In addition, mobile interventions can present a promising option where specialized face-to-face treatments are not available. Finally, EMI facilitate the examination of whether changes in putative psychological mechanisms ultimately result in changes in the symptoms they are supposed to be causing (i.e., interventionist causal model approach), therefore contributing to a better understanding of the mechanisms of change underlying CBTv [27]. A recent systematic review on EMI for people with psychotic disorders reported generally positive acceptability and feasibility ratings and provided promising evidence of improved clinical outcomes [28]. A first symptom-specific EMI trial for adults with persistent and distressing voices demonstrated its potential for improving comping with voices [29].

The main hypotheses of the current study are as follows: First, an 8-week treatment as usual (TAU) + CBTv-based EMI is more effective in reducing voice-related distress compared with TAU only. Second, the improvement attributable to the CBTv-based EMI will be maintained during the 6-month follow-up.

### Trial design {8}

This is a prospective, multicenter, assessor-blinded, two-armed, parallel-group, superiority RCT, using a 1:1 allocation. After providing written informed consent, participants will undergo a baseline assessment (T0) followed by a 9-day EMA. Afterwards, participants will be randomized to the intervention group or the control group. For the next 8 weeks, the intervention group will receive a CBTv-based EMI in addition to TAU, while the control group will receive TAU only. Afterwards, both groups will undergo another 9-day EMA, followed by a 3-month follow-up assessment (T1), and a 6-month follow-up assessment (T2). Figure 1 displays the Consolidated Standards of Reporting Trials (CONSORT) flow diagram of the study procedure.

**Fig. 1 Fig1:**
[figure not shown]
Illustration of the participant flow through the study. EMI, Ecological Momentary Intervention; CBTv, cognitive behavioral therapy for voices; TAU, treatment as usual

## Methods: participants, interventions, and outcomes

### Study setting {9}

Participants will be recruited from the following psychiatric clinics, located in the Canton of Bern, Switzerland: (1) Universitätsklinik für Kinder- und Jugendpsychiatrie und Psychotherapie, Universitäre Psychiatrische Dienste Bern (University Hospital for Child and Adolescent Psychiatry and Psychotherapy, University Psychiatric Services Bern); (2) Universitätsklinik für Psychiatrie und Psychothearpie, Universitäre Psychiatrische Dienste Bern (University Hospital for Psychiatry and Psychotherapy, University Psychiatric Services Bern); (3) Privatklinik Wyss in Münchenbuchsee (Private Psychiatric Clinic Wyss); (4) Privatklinik Meiringen (Private Psychiatric Clinic Meiringen); and (5) Psychiatriezentrum Münsingen (Psychiatry Center Münsingen). Additionally, participants will be recruited from local psychiatric or psychological private practices as well as via the webpage www.online-therapy.ch from the University of Bern, relevant internet forums, and advertisements in print and social media.

### Eligibility criteria {10}

Participants meeting the following criteria will be included in the trial: (1) aged 14 to 25 years; (2) experiencing current and persisting voices defined as a score of 1 (“voices occur at least once a week”) or above on the frequency item (no. 1) of the Psychotic Symptom Rating Scales-Auditory Hallucinations subscale (PSYRATS-AH) [30]; (3) experiencing distress due to voices, defined as a score of 2 (“a minority of voices is distressing (< 50%)”/“voices are moderately distressing”) or above on either of the distress items—amount of distress (no. 8) or intensity of distress (no. 9)—of the PSYRATS-AH; and (4) written informed consent. Exclusion criteria are as follows: (1) insufficient conduct of German; (2) hearing voices with an organic cause (e.g., brain disease or injury); (3) acute risk of harm to self or others that requires immediate crisis intervention; (4) inability to give informed consent and/or adhere with the study procedure; (5) currently receiving face-to-face psychological therapy that specifically addresses hearing voices (e.g., CBTp); and (6) intellectual disability.

### Who will take informed consent? {26a}

Potential participants will be contacted by a member of the research team to provide a participant information sheet with sufficient information to make an informed decision, discuss the study, screen for eligibility, and obtain written informed consent. The meeting can take place in person or by phone. If the latter is the case, the participant information sheet and informed consent form will be sent by email. The researchers will make sure that potential participants have enough time to consider whether or not they want to participate in the study. According to Swiss law, adolescents from the age of 14 are allowed to sign the informed consent form themselves (no parental consent needed). For participants aged 14–17 years, parents or legal guardians will receive a separate participant information sheet.

### Additional consent provisions for collection and use of participant data and biological specimens {26b}

Not applicable—this trial does not involve collecting biological specimens.

### Interventions

#### Explanation for the choice of comparators {6b}

In this two-armed, parallel group, superiority RCT, TAU was chosen as the control group in order to examine whether CBTv-based EMI added to standard treatment is superior to standard treatment alone in reducing voice-related distress. Thereby, TAU was defined as including both no psychological/psychiatric treatment at all and any form of psychological/psychiatric treatment. While this strategy will result in a heterogeneous TAU group requiring detailed description, it has the advantage that youth who are not in treatment yet and for whom the smartphone-based intervention represents an attractive, low-intensity option can also be included in the study.

#### Intervention description {11a}

##### CBTv-based EMI

Participants allocated to the intervention group will receive 8 weeks of EMI based on CBTv in addition to TAU. The EMI will have a time-contingent design with a semi-random sampling schedule. Participants will be prompted twice a day to complete an EMA survey on their smartphone. Prompts will occur randomly within two time intervals occurring between 8:00am and 12:00pm and between 2:30pm and 6:30pm, respectively. Each EMA survey will take approx. 2–3 min to complete and assesses the occurrence of voices since the previous assessment; perceived distress of voices; beliefs about voices; passive, aggressive, and assertive relating to voices; whether they had social contact since the last assessment; passive, aggressive, and assertive relating to other people; self-esteem; whether they have used the therapeutic strategies proposed at the previous assessment; and perceived helpfulness of the proposed therapeutic strategies or reasons of non-use, respectively. A full list of the items is provided in Additional file 1. Based on the individual responses to the EMA survey, participants will receive one intervention proposal per assessment to try out until the next assessment.

The EMA and EMI are implemented using the web-based software program ASMO (Ger.; Assessment und Monitoring psychischer Gesundheit; asmo.online) developed by the Center for Psychotherapy Research, University Hospital Heidelberg, Germany [31]. The software has been used in numerous collaborative projects (e.g., [32, 33]) and will be adapted to meet the requirements of the current trial. As soon as participants are registered on the program, they are automatically notified using text messaging via the Short Message Service (SMS) whenever an EMA is due. They can click on the link in the SMS and are automatically directed to the internet platform where they complete the EMA survey. A software program automatically analyzes the incoming messages based on a pre-defined algorithm (e.g., with respect to the occurrence of voices since the last assessment or the participant’s momentary (functional versus dysfunctional) beliefs about voices). Based on this evaluation, the program automatically selects a feedback message from a pool of pre-formulated statements and the message is presented to the participant in response to their report. In addition, participants can access the internet platform to receive therapeutic information and exercises at any time.

Before the start of the 8-week EMI, a single, individual introduction session will take place. In this session, participants will get familiarized with the rationale of the CBTv and receive a technical introduction to ensure they understand how to use the EMI. They will be encouraged to contact the research team whenever they experience difficulties during the intervention phase. After the 8-week EMI, a single, individual closing session will take place in order to explore what participants have learnt from the intervention and what they will take away for the future.

The intervention and the introduction and closing sessions are informed by the “Overcoming Distressing Voices” self-help book by [name] [34]. Specifically, Chapter 1 (“Understanding voices”), Chapter 2 (“Self-esteem and hearing voices”), Chapter 3 (“Relationships with voices and other people”), Chapter 4 (“Coping with voices”), Chapter 5 (“Changing beliefs about voices”), Chapter 6 (“Overcoming low self-esteem and distressing voices”), Chapter 7 (“Changing our relationship with voices and other people”), and Chapter 8 (“Moving forwards”) are translated to German and adapted for the use in the current study.

##### Treatment as usual (TAU)

TAU can include both no psychological/psychiatric treatment at all and any form of psychological/psychiatric treatment. No restrictions are imposed on the setting (i.e., inpatient vs. outpatient treatment) or type of treatment (i.e., psychological or pharmacological). Treatment may include the following elements: psychiatric case management, psychotropic medication, supportive counseling sessions, psychosocial interventions (e.g., social work, peer support), and individual, family, or group psychological therapies. Detailed information on the type and extent of the TAU at baseline (T0) as well as on changes in TAU over the study period (T1, T2) will be collected.

#### Criteria for discontinuing or modifying allocated interventions {11b}

Participants can be excluded from the study if the data of the baseline EMA reveals that voices primarily occur under the influence of alcohol and/or drug use or if further participation would pose a risk to them.

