#### EMA

The two EMA periods will last 9 days each and have a time-contingent design with a semi-random sampling schedule. Participants will receive ten text messages a day between 8:00am and 10:30pm, prompting them to complete an EMA survey. Each prompt will take place randomly within equal intervals of 60 min, with 30 min between intervals in order to prevent prompts occurring too close together. Each EMA survey takes approximately 2–3 min to complete and assesses sleeping problems (only in the first survey of the day); affective state; self-esteem; the occurrence of voices since the previous assessment; perceived distress of voices; beliefs about voices; passive, aggressive, and assertive relating to voices; social contact since the last assessment; passive, aggressive, and assertive relating to other people; and dissociative experiences, traumatic memories, non-suicidal self-injury, suicidal thoughts, and alcohol and drug consumption since the last assessment. A full list of the EMA items is provided in Additional file 1.

Before the baseline EMA, participants will be instructed how to use the EMA and practice its usage by going through a survey to ensure that each item is understood and appropriately rated. They will be given a written confirmation of participation in the study, which can be presented to teachers at school or supervisors at work if required. Participants will be encouraged to contact the research team immediately if they have any questions or technical issues related to the EMA.

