## Statistical methods

### Statistical methods for primary and secondary outcomes {20a}

Descriptive statistics within each randomized group will be presented for all variables assessed at baseline (T0), 3-month follow-up (T1), and 6-month follow-up (T2). To examine the effect of CBTv-based EMI on the primary outcome of voice distress (PSYRATS-AH Distress), multilevel regression models will be applied, with the participants’ ID as random, as well as group allocation (TAU + CBTv-based EMI versus TAU), time (T0, T1, T2), and PSYRATS-AH Distress at baseline as fixed effects. Multilevel modeling is advantageous over traditional methods of repeated-measures analysis, as it uses all available data and is unaffected by randomly missing data (135). The same approach will be used to analyze the effects of the CBTv-based EMI on secondary and other pre-specified outcomes. All analyses will be run based on the intention-to-treat principal (ITT) and be adjusted for confounding variables (e.g., sex, age). Standardized effect sizes will be reported. If needed, significance level adjustment will be applied to prevent accumulation of the type I error. Statistical analyses will be carried out using Stata Statistical Software [53] or R [85].

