### Methods in analysis to handle protocol non-adherence and any statistical methods to handle missing data {20c}

All statistical analyses will be run based on the ITT principal where all participants who are randomized are included in the analyses according to their group allocation, regardless of whether they completed the study or terminated it early. Since multilevel models can handle missing observations due to dropout (assuming data are missing at random), imputation of missing values will not be needed.

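### The section 11b risk rule removes a participant from the study rather than from the intervention, at any time, so T1 can be lost after randomisation for a reason probably related to outcome

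*Protocol article*

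**What the plan says.** Section 11b of the protocol article, headed as criteria for stopping or changing the allocated intervention, consists of one sentence with two grounds.

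- **Substance use:** "Participants can be excluded from the study if the data of the baseline EMA reveals that voices primarily occur under the influence of alcohol" or drugs. This rests on the baseline EMA, which comes before allocation (Trial design, section 8): "participants will undergo a baseline assessment (T0) followed by a 9-day EMA. Afterwards, participants will be randomized to the intervention group or the control group".
- **Risk:** "or if further participation would pose a risk to them". This has its own conditional clause, is not tied to the baseline EMA, and carries no time limit.

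Three other places bear on it:

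- **After the 8 weeks** (section 8): "both groups will undergo another 9-day EMA, followed by a 3-month follow-up assessment (T1"). That second EMA asks about "non-suicidal self-injury, suicidal thoughts, and alcohol and drug consumption since the last assessment" (EMA subsection of section 18a).
- **Primary model** (section 20a): the named terms are a random effect for participant, then "group allocation (TAU + CBTv-based EMI versus TAU), time (T0, T1, T2), and PSYRATS-AH Distress at baseline as fixed effects", with adjustment for confounders of which sex and age are given as examples.
- **Missing data** (section 20c): all randomised participants are analysed, early terminators included. The multilevel model is relied on ("assuming data are missing at random), imputation of missing values will not be needed").

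**The concern.** Stopping an intervention and ending follow-up are different actions. The text provides only the second: no rule takes a participant off the EMI and keeps them in assessment. Acute risk is already an entry exclusion (section 10), so the risk ground mainly covers deterioration that appears later, including the weeks between allocation and T1.

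The primary outcome is the change in PSYRATS-AH Distress from T0 to T1. Anyone excluded in between has no primary outcome, and also no T2 value for the hypothesis that improvement is maintained. In young people with distressing voices, clinical risk is plausibly linked to worse distress, so the missing values would tend to be the poor ones. If this happened more often in the EMI arm, that arm would look better than it is. If it happened equally in both arms, the loss would be one of information.

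**Working it through.** **1. Does the rule reach randomised participants?** The substance ground does not, because its data precede allocation. The risk ground does: it refers to continuing in the study and sets no time window. If it were read as applying only before allocation, section 11b would contain no criterion for stopping an allocated intervention at all.

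**2. Does the analysis recover the lost value?** Intention to treat keeps the T0 record but cannot supply an uncollected T1. Table 1 schedules no PSYRATS-AH between T0 and T1, and post-baseline risk is not among the terms named in section 20a. If risk reflects worsening since T0, nothing in the named model carries that information.

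**3. The plan's sample size.** Inputs from section 14: f = 0.25, power 0.80, alpha .05. For two groups d = 2f = 0.5. A noncentral F test with noncentrality f²N and 1 numerator degree of freedom gives power 0.801 at N = 128, which reproduces the stated figure. Then 128 × 1.2 = 153.6, rounded up to 154. The margin for loss is 154 − 128 = 26, and 26/154 = 16.9%. Each avoidable exclusion uses one of these 26.

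**4. Size of the bias.** All exclusion rates are assumed. Set-up: true effect 0, outcome SD 1, T0–T1 correlation r, and logistic exclusion on the standardised residual change. The log-odds are 0.5, 1.0 or 1.5 per SD worse, so the odds of exclusion rise by exp(0.5) = 1.6 to exp(1.5) = 4.5 per SD. The analysis is a baseline-adjusted regression with 2,000,000 simulated per arm. Negative values favour EMI.

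| Excluded, EMI vs TAU | r = 0.5 (log-odds 0.5 / 1.0 / 1.5) | r = 0.7 (log-odds 0.5 / 1.0 / 1.5) |
|---|---|---|
| 3% vs 0% | −0.014 / −0.026 / −0.035 | −0.011 / −0.020 / −0.028 |
| 5% vs 1% | −0.018 / −0.032 / −0.044 | −0.014 / −0.028 / −0.036 |
| 10% vs 2% | −0.034 / −0.062 / −0.083 | −0.028 / −0.051 / −0.068 |

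With equal rates (5% vs 5%, 10% vs 10%) the bias lies between −0.0015 and +0.0013.

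*Hand check:* bias ≈ rate difference × log-odds × residual SD, where residual SD = √(1 − r²). At r = 0.5 this is √0.75 = 0.87. With log-odds 1.0:

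- 3% vs 0%: 0.03 × 0.87 = 0.026 (simulated 0.026).
- 10% vs 2%: 0.08 × 0.87 = 0.070 (simulated 0.062).

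*Cruder bound:* if a share e of the EMI arm only is excluded, and those excluded are k SD worse than those retained in a way observed data do not predict, the bias is e × k. For e from 2% to 10% and k from 0.5 to 1.5, this runs from 0.02 × 0.5 = 0.01 SD to 0.10 × 1.5 = 0.15 SD.

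**5. Two-sided type I error.** 20,000 simulated trials, 77 per arm, r = 0.6, log-odds 0.5 / 1.0, Monte Carlo standard error about 0.0015:

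| Excluded, EMI vs TAU | Type I error |
|---|---|
| none | 0.050 / 0.052 |
| 3% vs 0% | 0.051 / 0.051 |
| 5% vs 1% | 0.052 / 0.054 |
| 10% vs 2% | 0.056 / 0.073 |
| 5% vs 5% | 0.050 / 0.048 |

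**The case against.** The strongest reply is that this is one permissive sentence in a condensed article under a standard SPIRIT heading. The full protocol (version 1.2) is not shown and may say what happens to T1 and T2 after exclusion. That would answer a complaint about missing detail. The point here is that the rule which is stated acts on the wrong thing. A later analysis plan cannot restore values that were never collected.

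A second reply is that stopping is proper if taking part is itself the hazard. That is right, and the proposed wording keeps the exception. What changes is the default.

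A third is that the issue is handled elsewhere: all-randomised analysis (20c), retention efforts (18b), screening for acute risk at entry (10), and a 20% attrition allowance (14). These limit the numbers affected, but none of them supplies a missing T1 value.

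The objection on size has the most force. Bias needs unequal exclusion, and the documents do not say exclusion will be unequal. Both arms complete the EMA that contains the self-injury and suicidality items. The article's summary of the twice-daily EMI survey lists no such items, and its responses are processed automatically, so that survey is weak evidence of closer risk detection in the EMI arm. What remains is the introduction session, the invitation to report difficulties, and contact when EMI responses drop. The simulation assumes selection on unobserved change, so it shows what could happen, not what will. At 3% vs 0% and 5% vs 1% the type I error barely moves. The rate of 10% vs 2%, about 8 versus 1 or 2 of 77, has no support in the documents. Finally, the link between risk and voice distress is a reasonable inference that the protocol does not state, and its list of adjustment variables is open-ended.

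**Conclusion.** The concern holds for the risk ground. As written, it permits loss of the primary outcome after randomisation, for a reason probably related to that outcome, although T1 and T2 are already scheduled for everyone. The substance ground needs only a clarifying word.

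The likely effect is small. Against the targeted d of 0.5, a bias of 0.011 to 0.035 SD at 3% vs 0% is 2% to 7% of the effect, and 0.028 to 0.083 SD at 10% vs 2% is 6% to 17%. With equal exclusion there is essentially no bias, only lost information. These figures rest on assumed exclusion rates, an assumed strength of selection and T0–T1 correlations of 0.5 to 0.7. The direction towards EMI depends on more exclusions in that arm, which is possible but not stated. The change is worth making because it costs so little; leaving it would not invalidate the trial. Confidence is medium.

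**What to change.** Keep the clinical triggers and change what they stop. Suggested text for section 11b:

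> After randomisation, if continuing poses a risk to the participant, the EMI and/or EMA prompts are stopped or paused. T1 and T2 (at least the PSYRATS-AH) are still offered unless the participant withdraws consent or a clinician judges the assessment itself unsafe.

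Add that the substance check on baseline EMA data is made before allocation, as the sequence in section 8 already implies.

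The cost is protocol wording, a few follow-up contacts that would otherwise have been dropped, and a clinician's safety judgement before each of them. No new visits or measures are needed.
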